#### Pilot Procedures

We will use C4 decision support tool, which is an HTML-5 mobile web-based app that does not require device-specific configurations. Staff will provide participants with a web link to the decision-support app. When possible (ie, when a participant has a smartphone or other applicable device), staff will help participants preprogram the decision support app as both a bookmark and an icon on the participant’s device and the RA will give participants a brief tutorial on its use. Patients assigned to the experimental condition (High Decision Conflict + Decision Support and Low Decision Conflict + Decision Support) will be asked to use the bookmarked link to the decision-support website within the first 14 days (and thereafter as needed) during the study period. The routine care control group will be asked to use a bookmarked link to the frequently asked questions website on emtricitabine/tenofovir for PrEP. All groups will be compared on decision readiness and decision conflict at 14 days, self-reported PrEP initiation at 30 days, and PrEP adherence at 60 days postenrollment.

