#### Ottawa Decision Support Framework Adaptation

We will use inputs from the qualitative findings in aim 1, public health guidelines on PrEP, and the emtricitabine/tenofovir product monograph to tailor the ODSF for use in the Client-Centered Care Coordination (C4) PrEP decision support web-based app.

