#### Data Collection

Data on decision conflict and PrEP initiation will be generated by the participant from self-administered assessments via the decision-support web-based app. We will also collect finger-stick blood drops to measure adherence to HIV PrEP at 60-days postenrollment. We will use several sources of data in this study. The data sources are structured survey and blood draw.

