#### Risks of Unintentional Disclosure of Private Health Information

The greatest potential risk in this study was the potential for a breach of confidentiality which is most likely to occur in situations where the participant has opted to have the RA perform study procedures (eg, study description, informed consent, data collection) outside of one of the participating agencies, such as in their private home. The clinic sites are all equipped with private examination rooms that allow the participant and RA to discuss private health information without the risk of unauthorized persons overhearing protected information. To support participant autonomy and comfort, we will also designate the SMH Li Ka Shing Knowledge Institute as an alternative site for data collection. This site also has private spaces where study procedures can be performed. If a participant desires to complete study procedures in a nonclinic location, the RA cannot guarantee that what is discussed cannot be overheard by others who may be in the immediate vicinity either at a fixed distance away or moving around nearby.

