### Legal Implications of Unintentional Disclosure of Private Health Information

It is possible that the participants in this study could be engaged in social and/or legal contractual arrangements with others that may presume mutual monogamy, such as marriage. An unintentional disclosure of sexual behavior information, including same-sex behavior, could provide material evidence for litigation against the study participant by an allegedly injured party. This could have both legal and financial consequences for the study participants. This risk is more likely to occur during a visit outside of the clinical setting where others who are not bound by privacy regulations may be in close enough proximity to hear clinical discussions between the participant and the RA.

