All survey data were entered into Snap Professional software. Once the survey is complete (ie, the submit button is selected), the survey is uploaded automatically to the Snap web host. Before it reaches the web host, it must first travel through a secure socket layer (SSL), which is where the data is encrypted. Any partially completed surveys will undergo the same process and can be retrieved from the web host to complete at a later date. As soon as this transfer is complete, the survey and its data are automatically removed from the device. Data stored on the secure web host server will be deleted after study completion. Before deletion, the research team will confirm that all completed surveys have been downloaded to the SMH secure server. Once confirmed, the surveys will be deleted from the Snap webhost, and this will be documented in an Excel file. Again, both the Snap web host and SSL tunnel have undergone a TRA to ensure that the data transferred and stored remains encrypted and secure.

No identifying information (eg, name, address, phone number, place of employment) was collected in the behavioral survey. The behavioral survey data is maintained separately from the data file, which includes participants’ contact information to reduce the risk that survey responses are linked to participant identities. No identifying information is listed on the blood samples of the dried blood spots. The dried blood spot transport media will be labeled only with participant identification codes. ID codes will be used to match the emtricitabine/tenofovir concentration with the self-report data variables for each participant.

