###### Aim 2: Analysis Plan

To compare conditions, we will use analysis of covariance procedures. When we compare the 4 conditions, our primary interest will be the tests of participants who received the decision-support intervention versus the information-only control. We will test whether the decision quality, PrEP initiation, and PrEP adherence differ between conditions controlling for baseline decision-quality score. We did not conduct a power analysis to calculate sample size because we de-emphasized hypothesis testing in favor of generating effect size estimates to inform the development of a larger study.

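### The PrEP app icon and bookmark set up on participants' own devices are not covered by the plan's disclosure risks or safeguards

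*Protocol article*

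**What the plan says.** **The device procedure.** Pilot Procedures gives participants a web link to the decision-support tool. Where the participant has a smartphone or similar device, "staff will help participants preprogram the decision support app as both a bookmark and an icon". Ottawa Decision Support Framework Adaptation describes the tool as a "PrEP decision support web-based app". For the other arm, "The routine care control group will be asked to use a bookmarked link to the frequently asked questions website on emtricitabine/tenofovir for PrEP". The intervention arm is asked to use its link within the first 14 days and later as needed. Under Aim 2, Data Collection, decision conflict and PrEP initiation are recorded through "self-administered assessments via the decision-support web-based app".

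**The stated risk.** Risks of Unintentional Disclosure of Private Health Information says: "The greatest potential risk in this study was the potential for a breach of confidentiality". It places that breach mainly in study procedures that the research assistant carries out away from the participating agencies. Legal Implications of Unintentional Disclosure of Private Health Information adds: "An unintentional disclosure of sexual behavior information, including same-sex behavior, could provide material evidence for litigation against the study participant". It too considers this more likely at visits outside the clinic.

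**The stated protections.** Reminder About Risks of Disclosures Outside of Clinic Environments applies to participants who want consent or survey procedures done off-site. Patient Surveys and Confidentiality of Data and Information Storage say that once a survey has been uploaded, "the survey and its data are automatically removed from the device". The latter section also describes encryption in transit and rules out local storage of participant information.

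**The concern.** The study itself helps to put a lasting link to a PrEP tool or a PrEP page on a personal device. A partner or relative who sees the device could notice it. The article takes discovery by such people seriously: it describes possible legal and financial harm where a relationship presumes monogamy, and it keeps study information from the family or friends named as contacts. Yet its account of how disclosure could happen never reaches the device. At stake is whether participants can weigh this route before they accept the shortcut.

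**Working it through.** No arithmetic applies. The article states no sample-size derivation to reproduce ("We did not conduct a power analysis to calculate sample size because we de-emphasized hypothesis testing"), and the point depends on no numerical input. The check sets the device procedure beside the risk and protection text.

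1. **Is something left on the participant's own device?** Yes. Pilot Procedures describes an icon and a bookmark for the decision-support app, and a bookmarked link for controls. The only condition stated for the set-up is that a suitable device is available. The participant's preference is not mentioned as a condition, although staff help with the set-up rather than impose it.

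2. **Do the risk sections consider it?** No. The general disclosure section and the legal section develop one route, off-site procedures that others may overhear. Neither mentions an icon, a bookmark or another person seeing the device.

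3. **Do the protections cover it?**
   - The voluntariness section concerns participation and withdrawal in general.
   - The distress section concerns clinical support.
   - The reminder section concerns off-site consent and surveys.
   - The storage section limits contact details, encrypts survey data in transit, clears completed surveys from the device and rules out local storage of participant information.

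   The last group does protect the device with respect to survey answers. A shortcut holds no answers, so clearing the survey leaves the shortcut in place. The clearing step is described for the Snap survey; no equivalent is described for entries made in the decision-support app.

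4. **How many, and for how long?** Number of Subjects caps Aim 2 at 40, and the last assessment is at 60 days. These are ceilings. The article does not say how many participants will have a suitable device, accept the shortcut or keep it.

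5. **How revealing is it?** This cannot be determined. The tool is named C4, for Client-Centered Care Coordination, which contains neither HIV nor PrEP. The text shown under the icon or on either bookmark is not stated.

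**The case against.** The strongest reply is that this is an omission from a condensed article. The full protocol or the consent form may deal with phones, Process of Consent says the study is fully explained, and participants may be free to decline or delete a shortcut. That stands against any claim that participants will go unwarned. It does not remove the narrower point: the article itself states both a device procedure and an account of how disclosure is likely to arise, and the second does not take in the first.

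Several stronger readings are tempting, and the documents do not support them.

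- A reader might infer that the phone has no safeguard at all. Survey data are encrypted in transit and cleared from the device.
- A reader might infer a contradiction. The article says a breach is most likely, and legal harm more likely, off-site. Those are comparisons and do not deny other routes. Nor does clearing survey answers conflict with leaving a link that contains none.
- A reader might infer that every participant carries a visible PrEP label for 60 days. The label is unknown, set-up happens only where possible, and nothing requires the shortcut to be kept.
- A reader might infer that the app lacks access control. Payment for Participation and Risk for Financial Coercion both describe registration, the latter on the app itself, so some account step may exist.
- A reader might infer that fear of discovery lowers use and shrinks the effect estimate. Nothing in the article suggests avoidance, and both arms use a bookmark.
- A reader might want a count of participants exposed, or a comparison with home visits. The article gives no rate for either.

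**Conclusion.** The point holds as a modest, inexpensive improvement to participant protection. The article helps place PrEP-related shortcuts on personal devices, calls a confidentiality breach the greatest risk, and does not cover those shortcuts in its stated risks or safeguards. At most 40 participants over 60 days are concerned, and the number actually affected cannot be estimated. The conclusion assumes that the full protocol and consent form do not already deal with the shortcuts; if they do, the article's risk sections need only be aligned with them. The importance of the point also depends on the display label, and would be small if that label is already neutral. No effect on sample size, error rates, analysis or effect estimates is shown.

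**What to change.** - In Pilot Procedures, make the icon and bookmark the participant's choice, offered after a brief warning that other people may see them.
- Use a neutral display name, without HIV or PrEP, in both arms. For controls this means the name of the bookmark, since the page itself may be an existing website.
- Offer to remove the shortcuts at withdrawal and at the 60-day visit.
- Add device-level disclosure to Risks of Unintentional Disclosure of Private Health Information, and extend Reminder About Risks of Disclosures Outside of Clinic Environments to cover it.

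The cost is a few sentences of text and a labelling choice. Some participants may decline the shortcut, which would make the assigned site slightly less convenient to use. The article scheduled Aim 2 to start in May 2020, after the stage it reports, so the plan left room to make the change before the first Aim 2 participant enrolled.

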#### Data Collection

Data on decision conflict and PrEP initiation will be generated by the participant from self-administered assessments via the decision-support web-based app. We will also collect finger-stick blood drops to measure adherence to HIV PrEP at 60-days postenrollment. We will use several sources of data in this study. The data sources are structured survey and blood draw.

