#### Patient Surveys

RAs will send participants an email with the link to access the web-based structured survey, which will be programmed in Snap Professional software. All data were entered into Snap Professional software. Once the survey is complete (ie, the submit button is selected), the survey is uploaded automatically to the Snap web host. As soon as this transfer is complete, the survey and its data are automatically removed from the device. We will collect whole blood using a finger-stick procedure and use the microfluid sample for dried blood spot analysis.

#### Measures for Aim 2

In addition to basic demographic data that will be used to describe the sample (eg, age, gender, relationship status), we will use the measures summarized below to assess key variables necessary to address aim 2:

The sure test indicates *the probability that a patient experiences clinically significant decisional conflict.*The stage of decision making is a 4-6 item instrument. *Stage of decision making refers to the individual’s readiness to engage in decision making, progress in making a choice, and receptivity to considering or re-considering options.*The Decisional Conflict Scale is a 16-item tool.* The Decisional Conflict Scale (DCS) measures personal perceptions of: (1) uncertainty in choosing options, (2) modifiable factors contributing to uncertainty such as feeling uninformed, unclear about personal values and unsupported in decision making; and (3) effective decision making (in full version) such as feeling the choice is informed, values-based, likely to be implemented and expressing satisfaction with the choice.*The Decision Preparation Scale is a 10-item scale. *The scale assesses a patient’s perception of how useful a decision aid or other decision support intervention is in preparing the respondent to communicate with their practitioner at a consultation visit and making a health decision.*The Health Care Climate Questionnaire (HCCQ) is a 15-item questionnaire. *The HCCQ was designed to be used by patients to report their perceptions of their doctors or their team of health care providers*The PrEP Self-Regulation Questionnaire is a 15-item questionnaire that elicits information regarding why an individual may initiate and/or maintain PrEP usage.The PrEP Use Perceived Competence Scale is a 4-item scale for individuals who elect to use PrEP regarding their perceived confidence to adhere to their decision to use PrEP.

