#### Risk for Financial Coercion

We will also implement a modest, modular gratuity structure to be applied to participants who enroll and attempt to participate in the study. A Can $30 (US $22) cash gratuity will be offered for participation in the key informant interview. Health care providers who participate in the structured survey will receive Can $40 (US $29) cash gratuity. Subjects who participated in the pilot trial will receive a modest gratuity at enrollment when they register on the decision aid app via their smartphone device (Can $25 [US $18]), at day 30 when they complete the midpoint survey (Can $30 [US $22]), and at day 60 (Can $45 [US $32]) when they provide a blood sample for adherence assessment. Although the gratuity is very modest, it is possible that some individuals experiencing severe material and financial deprivation may be compelled to participate against their own volition in order to receive the modest gratuities offered.

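### Aim 2 gives app access and registration without limiting them by arm and collects two outcomes through the app, contradicting the FAQ-only control and the Snap survey route

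*Protocol article*

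**What the plan says.** **Statements that put participants on the app without naming an arm**
- Aim 2 Data Collection, on two of the outcomes: "Data on decision conflict and PrEP initiation will be generated by the participant from self-administered assessments via the decision-support web-based app".
- Pilot Procedures, before any arm is mentioned: "Staff will provide participants with a web link to the decision-support app". Where the device allows, "staff will help participants preprogram the decision support app as both a bookmark and an icon on the participant’s device", and the research assistant gives a short tutorial.
- Risk for Financial Coercion, on pilot subjects generally: they "will receive a modest gratuity at enrollment when they register on the decision aid app via their smartphone device".

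**Statements that point the other way**
- Pilot Procedures, on the comparator: "The routine care control group will be asked to use a bookmarked link to the frequently asked questions website on emtricitabine/tenofovir for PrEP". The experimental groups are the ones asked to use the decision-support site within 14 days.
- Aim 2: Analysis Plan names decision support versus an information-only control as the contrast of primary interest.
- The last sentence of Aim 2 Data Collection lists the data sources as a structured survey and a blood draw.
- Patient Surveys: "RAs will send participants an email with the link to access the web-based structured survey", programmed in Snap.
- Confidentiality of Data and Information Storage, and Data Handling, both place the survey data in Snap.
- Table 1 ties the first Aim 2 payment to the baseline survey and does not mention app registration.

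**The concern.** Pilot Procedures compares all groups on decision readiness and decision conflict at day 14, self-reported PrEP initiation at day 30 and adherence at day 60. If conflict and initiation are captured through the app, as Aim 2 Data Collection says, a control can supply them only by opening the app that defines the experimental arm. The document describes no control version, assessment-only module or access limit that would keep the decision-support content away from controls.

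The alternative is that the experimental arm answers in the app and controls answer in the Snap survey. Response setting and missing data could then differ by arm.

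The contrast between arms is what the pilot is for. The Analysis Plan explains the absence of a power calculation by saying that the pilot is meant to produce effect size estimates for a larger study. Control exposure would tend to pull that estimate toward zero. A difference in platform could move it in either direction. With 40 participants, neither could be reliably adjusted away afterwards.

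**Working it through.** The document gives no power, effect size or derivation of n = 40, so there is no figure to reproduce. The check is mainly textual.

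**1. The statements side by side**

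| Item | One statement | Conflicting statement |
|---|---|---|
| Who gets the app | Link, bookmark or icon and tutorial for participants, no arm named (Pilot Procedures); pilot subjects register at enrollment (Risk for Financial Coercion) | Controls are asked to use the FAQ site (Pilot Procedures); information-only control (Aim 2: Analysis Plan) |
| Route for conflict and initiation data | The app (Aim 2 Data Collection) | Emailed Snap survey (Patient Surveys); all survey data in Snap (Confidentiality of Data and Information Storage; Data Handling) |
| First payment | Can $25 on app registration (Risk for Financial Coercion) | Can $20 for the baseline survey (Table 1) |
| All payments | 25 + 30 + 45 = Can $100, none at day 14 | 20 + 30 + 30 + 40 = Can $120, including day 14 |

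**2. Which outcomes are affected.** The app sentence covers decision conflict and PrEP initiation. Day-60 adherence is measured from finger-stick blood, so its collection does not depend on the app.

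**3. What exposure would do, as an illustration.** Let c be the share of controls who use the tool and gain its full effect. Then:

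- observed d = true d × (1 − c)
- n per arm for a later trial = 2(1.960 + 0.842)² / d² ≈ 15.70 / d² (two-sided 5%, 80% power)
- growth in n = 1 / (1 − c)²

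The document gives none of true d, c, alpha or power. With d = 0.50 assumed:

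| c | Observed d | n per arm planned from it | Growth |
|---|---|---|---|
| 0 | 0.50 | 63 | 1 |
| 25% | 0.375 | 112 | 1.78 |
| 50% | 0.25 | 252 | 4 |
| 75% | 0.125 | 1005 | 16 |

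**4. Against the pilot's own precision.** With n = 40 (Number of Subjects) and 1:1 allocation assumed, SE(d) ≈ √(2/20) = 0.316. The 95% half-width is 1.96 × 0.316 ≈ 0.62. The shift at c = 25% is 0.50 − 0.375 = 0.125, well inside that. Sampling error would therefore hide the shift in the data, but the shift is systematic and would carry into the next trial's planning.

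**The case against.** A reader might infer that controls will receive the experimental tool and that the estimate will be diluted. The document does not support that, for these reasons.

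- **Use is assigned by arm.** Pilot Procedures asks the experimental groups to use the decision-support site and controls to use the FAQ site. The unrestricted sentences introduce the tool just before this, and the bookmark in the experimental instruction may refer back to that set-up. This is a fair reading of Pilot Procedures, but it does not explain the app-based data collection or the paid registration of pilot subjects.
- **Most of the text points to Snap.** The end of Aim 2 Data Collection, Patient Surveys, the confidentiality section and Data Handling all fit one Snap survey for both arms, and the app sentence is the outlier. An assessment page or survey link that does not open the decision aid is also possible. This stands: exposure and mixed platforms are not the only two readings.
- **The payment passage is weak evidence.** It sits in a risk section and conflicts with Table 1, which already has the baseline-survey payment. This stands. It makes the payment a further item to reconcile, not proof of control exposure.
- **The size rests on assumptions.** This also stands: c, d and full benefit in exposed controls are all assumed.
- **An article may leave the app's structure to the full protocol.** True, but the point here is not a missing detail. The article makes positive statements about access and data route that conflict with each other.

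**Conclusion.** The point holds as a contradiction that carries a risk of bias. App access, set-up, tutorial and paid registration are not limited by arm, and two outcomes are collected through the app. This conflicts with the FAQ-only control, the Snap survey route and Table 1. Staff following one set of statements would run a different comparison from staff following the other.

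Actual control use, and so any dilution, cannot be derived from the document. The dilution figures (observed d of 0.375 at c = 25% and 0.25 at c = 50%) assume d = 0.50 and full benefit in exposed controls, and they show sensitivity only. If the arms answered on different platforms, bias would be possible but not certain, and its direction is unknown. The adherence measurement is not tied to the app, although control exposure could still affect the adherence comparison.

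This should be settled before Aim 2 enrolls, because treatment separation in the contrast of primary interest depends on it.

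**What to change.** - **Aim 2 Data Collection:** collect self-reported decision readiness and decision conflict (day 14) and PrEP initiation (day 30) in both arms through the same Snap survey, outside the app. Keep day-60 adherence by dried blood spot.
- **Pilot Procedures:** restrict the app link, bookmark or icon set-up and tutorial to the experimental arm. Give controls equivalent set-up help for the FAQ link.
- **Risk for Financial Coercion:** align the enrollment payment with the baseline-survey payment in Table 1, so that it no longer depends on app registration.
- **Monitoring of separation:** record any control access to the app, so that contamination can be reported alongside the effect size.

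The cost is a wording change and an access control on the app. The Snap survey is already planned and the baseline payment is already in Table 1. The article gives Aim 2 as scheduled to start in May 2020, so no Aim 2 data are affected if the change is made before then.
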